## Abstract

Currently one-third of children in the United States have overweight or obesity (OW/OB). The goal of Healthy People 2020 is to reduce the proportion of children with OW/OB and increase the proportion of primary care visits that include nutrition and weight-related counseling. Unfortunately, many health care providers find it difficult to offer effective weight-related counseling and treatment in the primary care setting. Therefore, new models of care are needed that allow a greater proportion of children with OW/OB and their parents to access care and receive quality weight management treatment. The current paper describes the GOT Doc study which is designed to test the effectiveness of a Guided Self-Help (GSH) model of obesity treatment that can be delivered in the primary care setting compared to a traditional Family-Based Behavioral weight loss treatment (FBT) delivered at an academic center. We will assess the impact of this program on attendance (access to care) and changes in child BMI percentile/z-score. We will also examine the impact of this treatment model on change in child lifestyle behaviors, parent support behaviors, and parent self-efficacy and empowerment to make behavior change. Finally, we will assess the cost-effectiveness of this model on changes in child BMI percentile/z-score. We believe the GSH intervention will be a cost-effective model of obesity management that can be implemented in community practices around the country, thereby increasing access to treatment for a broader proportion of our population and decreasing rates of childhood obesity.

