## Introduction

1

Currently, one in three children in the United States aged 6–19 years have overweight or obesity, with higher rates among Hispanic and African-American children [1]. Because of the many medical and social co-morbidities [[2], [3], [4], [5], [6]] children with overweight/obesity (OW/OB) incur greater medical costs from frequent lab studies [7], sick visits, and utilization of mental health services [8]. While prevention is necessary, widely available and effective treatments are also needed to help those who are already on the path towards greater health care utilization.

The goal of Healthy People 2020 is to decrease the proportion of children with OW/OB and increase the proportion of primary care visits that include nutrition and weight-related counseling [9]. The Early and Periodic Screening, Diagnosis, and Treatment program (EPSDT) for children enrolled in Medicaid also recommends nutrition counseling at each well-child visit [10]. While primary care providers (PCPs) have been identified as key players in the treatment and prevention of obesity by several national groups [[11], [12], [13]] they often report low confidence in their ability to counsel on this topic, as well as a lack of time and resources [14,15]. The U.S. Preventive Services Task Force (USPSTF) has also noted that moderate intensity counseling may not be deliverable by PCPs within the confines of the current well-child visit, and that these children should be referred to intensive counseling or behavioral interventions to assist with weight loss [16]. Thus, if we are to follow national mandates to provide easily accessible and effective obesity-related treatment, other care models need to be developed.

Current gold-standard treatment for obesity involves family-based behavioral therapy (FBT). These programs are intensive, requiring up to 26 h of treatment over 6 months, and are typically located at tertiary care academic centers. However access to these programs can be difficult due to limits on capacity and location [17]. Furthermore, lack of flexibility in scheduling makes it difficult for families to attend weekly group sessions [17]. In one study, only 28% of the families who were offered this treatment enrolled, and only 63% of those families completed the intervention [18].

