We developed a Guided Self-Help (GSH) model of obesity management which is shorter in duration, could be delivered in the primary care setting, and has been shown to be equally effective as FBT [19]. GSH provides structured behavioral management for obesity treatment and is designed as a practical tool for health care providers to implement in the primary care office. Although the program is self-directed, GSH programs offer structure to promote treatment compliance and application, as is suggested by the Expert Committee Recommendations for Stage 2 treatment [12]. Frequency and intensity of visits are also realistic for the primary care setting and resembles Medicare coverage for adults.

The goal of this study is to test whether implementation of a GSH model of obesity treatment in the primary care setting can increase access for families to effective obesity treatment and decrease child BMI percentile/z-score. Given the need to increase access and availability of effective obesity treatment in the community, this intervention may provide useful information regarding the structure of such efforts.

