Medical Record Abstraction: At the end of the study period, de-identified information on patients with OW/OB who signed consent but did not complete the assessment or enrollment process will be obtained to determine if there were differences between those who enrolled vs. those who did not. For those enrolled in the study, information will be gathered regarding frequency of patient weight-related visits (to the PCP or a dietitian) and other health care utilization (including referrals, medications, hospitalizations).

Cost-effectiveness measures. Cost effectiveness is of interest in this trial due to the potential to replicate the proposed GSH model in other primary care settings. The primary perspective for this cost effectiveness analysis will be the societal perspective which captures the broadest range of costs that are pertinent [43]. From a societal perspective, the delivery costs for the intervention arm will include reproduction of intervention study materials, distribution of study materials, intervention staff/coaching time for counseling and follow-up, administrative staff time, patient time and expenditures to receive the intervention, and IT support. Research development and research related overhead costs will be excluded from the estimate of the intervention costs.

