### Obesity management by the PCP prior to randomization

4.1

All clinics within the CPCMG network utilize the EPIC electronic health record (EHR) and have a basic obesity management tool for children. This tool includes: 1) alerts to physicians to address and document weight status in all children older than 2 years with OW/OB; 2) prompts to assess risk for obesity-related medical co-morbidities and relevant family history; 3) a tool to facilitate efficient assessment of parent readiness to make behavior changes; 4) a focused menu of options of strategies for weight loss; 5) alerts to obtain appropriate labs, schedule follow-up visits, and make sub-specialty referrals when necessary; and 6) links to handouts and referrals to weight loss treatment options at the tertiary care center. To determine whether parents are ready to engage in obesity treatment, the PCP (prompted by the EHR) will ask parents of all identified children 3 motivation questions: “On a scale of 1–5 with 1 being ‘not important’ and 5 being ‘very important’, how important is it for you to make changes to help your child lose weight at this time?”; “On a scale of 1–5 with 1 being ‘not confident’ and 5 being ‘very confident’, how confident are you that you can help your child lose weight at this time?”; and “On a scale of 1–5 with 1 being ‘not motivated at all’ and 5 being ‘very motivated’, how motivated are you to help your child lose weight at this time?”. These questions are based on the transtheoretical model of behavior change [45], and patients who report higher scores on these questions have reported greater success in weight loss activities [21,46,47]. Parents who report a 3 or higher on any question will be told about the study and asked if their name and contact information can be sent to the study coordinator. If the parent agrees, referrals to the study coordinator will occur via a link in the EHR and/or in person (if she is in the office that day). The study coordinator will contact the family and screen for eligibility. Once families have completed the consent process and baseline assessments, they will be randomized to the intervention (GSH) or usual care (FBT) group. Randomization will be conducted with a random number generator independent of the investigators and physicians. Participants will be informed of both intervention possibilities to ensure their commitment to both. Due to the clear differences in treatment groups, participants will not be blinded to the treatment arms.

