5.3. Power Analysis: For this trial, sample size estimates took attrition into account. Our first primary hypothesis is that a greater proportion of families in the intervention group will enter into and attend behavioral treatment for obesity. However, there was lack of evidence from previous studies to conduct a power analysis with this outcome. Therefore, power analyses were based on changes in BMI z-score (our second primary outcome) that was supported by observations in the GSH pilot which estimated a decrease in BMI z-score d = |1.71–1.50|/.30 = 0.667. Empirical power estimates were assessed by generating multivariate random samples that were matched to the expected BMI z-score for each condition and variability over time as observed in our pilot study. We expected decreases in BMI z-score of 0.10 among those enrolling in GSH, and a slight increase of 0.05 in BMI z-score in the usual care group. Each of 1000 simulated data sets was analyzed using a LME (random intercepts: patients within clinics) and specific output saved (e.g., standardized regression coefficients, p-values). The percentage of datasets with significant effects (i.e., p < 0.05) for the primary hypothesis comparing GSH vs. usual care provided a simulation-based estimate of power for the primary hypothesis. With a median between-group effect of −0.39 (s d. = 0.13) across 1000 data sets, the planned design would provide greater than 0.82 power for detecting the effect with allowance for up to 20% lost to follow up [72]. We allow up to 20% loss to follow-up to maintain the integrity of the sample for data analysis, and have been able to limit our loss to follow-up in previous trials to 13–18% of the sample. Given these parameters, we estimated that we would need to recruit 200 families into the trial, 100 in GSH and 100 in FBT. With a sample of 200 to support between-group comparisons of BMI percentile/z-score, we estimate we will have power >0.95 to detect a difference in the proportion of sessions attended in a generalized linear model (binomial) with two-sided alpha <0.05 given that we expect >85% attendance in GSH and 60% attendance in FBT. All analyses of primary outcomes will use an intention to treat sample with analyses of all participants who provided both baseline and post-treatment assessments.

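### The first primary hypothesis and the access goal are tested only among families who consented and accepted randomisation to either programme: starting and attending can be compared, uptake of the offer cannot

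*Protocol article*

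**What the plan says.** **The aim.** The Introduction asks whether GSH in primary care "can increase access for families to effective obesity treatment and decrease child BMI percentile/z-score". The Abstract ties the measure to the goal: "We will assess the impact of this program on attendance (access to care) and changes in child BMI percentile/z-score". Section 5.3 puts the first primary hypothesis as "a greater proportion of families in the intervention group will enter into and attend behavioral treatment for obesity".

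**The problem as the plan sees it.** The Introduction attributes poor access to family-based treatment (FBT) to capacity, location and inflexible scheduling. It cites one study in which "only 28% of the families who were offered this treatment enrolled, and only 63% of those families completed the intervention".

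**Who is randomised.** Section 3.4 refers families who are interested in a weight control programme. Section 4.1 requires a score of at least 3 on any one of three motivation questions, and then: "Once families have completed the consent process and baseline assessments, they will be randomized to the intervention (GSH) or usual care (FBT) group". Families hear about both programmes beforehand ("Participants will be informed of both intervention possibilities to ensure their commitment to both"). FBT means 16 weekly and then 4 biweekly group sessions in La Jolla (section 4.3).

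**What is analysed.** Section 5.1 compares the proportion of sessions attended with a binomial generalised linear model. Section 5.3 restricts all primary analyses to participants with both a baseline and a post-treatment assessment.

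**Who else is looked at.** Under Medical Record Abstraction, section 3.6.1 plans to obtain "de-identified information on patients with OW/OB who signed consent but did not complete the assessment or enrollment process" and to compare those families with the enrolled ones.

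**The concern.** The hypothesis speaks of entering treatment, and the goal speaks of access. Allocation comes after every step at which a family can decline the offer. A family that could manage short visits at its own clinic, but not weekly travel to the academic centre, has reason to refuse randomisation, and refusal leaves it outside the comparison. That is a family the primary-care model is meant to reach.

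Two misreadings are at stake. If attendance is similar in the arms, a real gain in uptake could be dismissed although it was never measured. If attendance is better with GSH, the result could be reported as wider access in the community although it describes only families who accepted either programme.

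A second problem lies inside the trial. A family that never starts is plausibly also one that misses the month 6 visit. If it is then left out of the attendance analysis, the entry part of the hypothesis is lost even where the design could have tested it.

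**Working it through.** **Step 1. Reproduce the plan's own figure.** Section 5.3 gives power above 0.95 for 85% versus 60% attendance with 200 families and two-sided alpha 0.05. Treat each family as one binary unit, with mean proportion 0.725:

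power = Φ{[0.25 − 1.96·√(2·0.725·0.275/n)] / √[(0.85·0.15 + 0.60·0.40)/n]}

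- n = 100 per arm: (0.25 − 0.1238)/0.0606 = 2.08, power 0.981.
- n = 80 per arm (20% lost): (0.25 − 0.1384)/0.0678 = 1.65, power 0.950.

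Treating attendance as a family-level proportion of 14 or 20 sessions, power is at least 0.985 (100 per arm) or 0.958 (80 per arm) even if sessions within a family are perfectly correlated. The stated power stands. It is power for attendance among randomised families.

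**Step 2. Find where the arms begin to differ.**

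| Step | Section | Contrast between arms? |
|---|---|---|
| Identified in the health record | 3.4 | No |
| Motivation score, interest, referral | 3.4, 4.1 | No |
| Screening, told of both programmes, consent, baseline | 3.4, 4.1 | No |
| Randomisation | 4.1 | Arms begin |
| Starting treatment | Table 1, 5.1 | Yes |
| Sessions attended | 5.1 | Yes |
| Post-treatment assessment | 5.3 | Yes, and it defines the analysis set |

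Uptake of the offer belongs to the first three rows, where no arm exists. The section 3.6.1 comparison reaches only families who signed consent. It contrasts enrolled with non-enrolled families, not arm with arm.

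**Step 3. What remains unknown about uptake.** Attendance per offered family = uptake × attendance among those who take it up. FBT uptake of 28% comes from the Introduction; attendance of 60% and 85% comes from section 5.3. GSH uptake is an assumption, as is applying the same attendance rates to whoever takes up the offer.

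FBT: 0.28 × 0.60 = 16.8%.

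| Assumed GSH uptake | GSH, per offered family | Difference |
|---|---|---|
| 28% | 0.28 × 0.85 = 23.8% | 7.0 points |
| 40% | 0.40 × 0.85 = 34.0% | 17.2 points |
| 50% | 0.50 × 0.85 = 42.5% | 25.7 points |
| 60% | 0.60 × 0.85 = 51.0% | 34.2 points |

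A perfectly run trial under this plan would be compatible with any row. A comparison of uptake at the point of offer would be a different study: against 28%, at 80% power, it needs 691, 244, 76 or 37 families per arm for GSH uptake of 35%, 40%, 50% or 60%.

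**Step 4. What can be compared.** Starting after randomisation is observable by arm. With 100 per arm and assumed starting rates, power is about 0.66 for 95% versus 85% and 0.90 for 95% versus 80%.

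**Step 5. Effect of the analysis set.** Read the 60% as the mean over all 100 FBT families, non-starters included. If k non-starters are dropped, the analysed mean is 60/(100 − k): 60/90 = 66.7% for k = 10, and 60/80 = 75.0% for k = 20, the full loss allowance. Against 85% in GSH with no one dropped, the difference falls from 25 to 18.3 or 10 points. The values of k are assumptions; the documents give no rate of non-starting.

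**The case against.** The strongest reply is that the plan says what it means by access. The Abstract equates it with attendance, section 5.1 analyses sessions attended, and the hypothesis concerns families already in an arm. Consent before allocation is the ordinary limit of an individually randomised trial. This largely stands. A reader might infer that the trial cannot show any access benefit, and the documents do not support that: a randomised family can attend no sessions, Table 1 schedules enrolment and attendance weekly, and the contrast is valid for those randomised.

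A reader might also take the commitment sentence in section 4.1 as an eligibility rule that excludes families unwilling to travel. It describes informing participants. The only commitment criterion in section 3.3 concerns assessment visits. Some families may consent hoping for GSH and then not attend FBT, and the trial would capture them. Even so, consenting to randomisation implies accepting either arm, so some selection remains, of unknown size.

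It is tempting to put a size on the gap from the cited study: 0.28 × 0.63 = 17.6% complete, so 72 of the 82.4 lost per 100 offered (87%) are lost before enrolment and 13% after it. This is illustrative only. It is one outside study, completion is not the same measure as sessions attended, and some of the 72 might decline GSH too.

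The Discussion is hedged: it says better attendance may allow wider access. And if the families lost are mainly those who would accept only GSH, the selection would tend to understate its benefit, not create a false one.

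On the analysis set, section 5.4 says mixed models use all available data. That describes the BMI models. Attendance is analysed by a different model, and the section 5.3 restriction covers every primary outcome.

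**Conclusion.** The concern holds as a mismatch between claim and population, not as an invalid comparison. The trial can compare starting and attending among families who showed interest, consented, completed baseline and accepted randomisation to either programme. It cannot estimate uptake among families offered treatment, and the section 3.6.1 records do not supply this.

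No magnitude for the uptake gap can be derived for this trial. The 7 to 34 point range rests on one cited uptake figure, the plan's expected attendance rates and assumed GSH uptake; it shows only that the quantity is left open. The analysis-set restriction is a separate and avoidable weakness. If non-starting is commoner in FBT and non-starters miss the month 6 visit, it would shrink the attendance difference. The attendance power calculation needs no change. The point should be fixed before results are reported, because it governs what may be concluded.

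**What to change.** 1. Restate the section 5.3 hypothesis and the Discussion's conclusion as starting and attending treatment among consenting families willing to accept either programme. The reference to entering treatment can stay if it is defined as starting after randomisation. Do not present the result as uptake or population access.
2. Analyse attendance in all randomised families, with non-starters at 0 sessions, whether or not they have a post-treatment assessment. Attendance is recorded at the sessions, so no extra data are needed.
3. Extend the section 3.6.1 comparison from families who signed consent to de-identified counts of all families referred through the health record, at each step up to randomisation. Record reasons for declining, including unwillingness to accept the FBT site or schedule. Families who decline before referral will still be missed.

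Questions at screening about willingness to start each programme are at most an optional supplement: stated willingness is a proxy, and parents will already have heard about the study from the primary care provider.

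The cost is a narrower headline claim, a change of wording, a wider record count and a minor ethics amendment. The sample size is unaffected.

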
### Intervention group: Guided Self-Help for pediatric weight loss

4.2

The GSH intervention will include 14 sessions over 6 months to mimic the structure of the proposed Medicare funding for obesity treatment for adults (www.cms.gov). These sessions will last 20 min, except for the first session which can last up to an hour, and take place in the clinic. During the first session, the family will receive a parent treatment manual and an age-appropriate child manual that covers several nutrition and physical activity topics as well as behavioral strategies. During the first treatment meeting, manuals are provided to families, and they are instructed to read each chapter prior to the next meeting. The purpose of the manual is to provide key components of gold-standard family-based behavioral therapy (FBT) [[48], [49], [50]] for childhood obesity in a self-help format. Parent manuals emphasize changing the behaviors of the family, and child manuals emphasize changing their own behaviors, in an age-appropriate manner.

In the first session, the health coach will review the structure of future meetings, review how to complete self-monitoring diaries, and set goals with the families. During subsequent sessions, the health coach will assess patient/parent readiness to engage in behavior change, assess barriers and facilitators to behavior change, engage in behavior change and problem solving, and provide feedback and accountability. The goals of the 20-min meetings are to: a) measure the child and parent's weight and reflect with the parent/child dyad on any eating or physical activity changes that may have influenced weight change (either up or down) between visits; b) clarify the content of the manuals; c) use problem-solving to address barriers to implementation of the behavioral strategies outlined in the manual; d) reinforce effort and success; and e) encourage parents and children to try new behavioral techniques. Parents and children will meet together with the health coach during these 6 months.

Dietary recommendations. GSH utilizes the Traffic Light Diet, which categorizes food by energy content into the three colors of the traffic light. Foods are classified into red, yellow and green based on caloric density and grams of sugar per serving; green foods (go) are low in calories and may be consumed in unlimited quantities; yellow foods (caution) have average nutritional value for foods within their food group and are to be eaten with caution; red foods (stop) are energy-dense and should be limited in quantity [[51], [52], [53], [54]]. Dietary recommendations encourage parents/children to count the number of servings consumed for each traffic light color (red, yellow and green). All reductions in energy intake are shaped over time and decreases in consumption of red foods are reinforced. Children will be encouraged to consume 1000–1200 kcals per day while parents will be encouraged to consume 1200–1400 kcals/day. Additional goals include increasing the number of family meals eaten together and increasing vegetable and fruit consumption.

Physical activity recommendations. GSH recommends increasing both lifestyle activity and structured exercise programs [[55], [56], [57]]. Lifestyle activity goals focus on building increased activity into typical, daily activities, such as walking or bicycling to school, and structured exercise goals stimulate routine, planned exercise. Parents and children are also instructed to decrease sedentary behaviors, such as TV watching, video games or computer usage outside of schoolwork. The goal is to engage in 90 min of physical activity on 5 out of 7 days of the week for children and at least 60 min on 5 out of 7 days of the week for parents.

Behavior change recommendations. Key elements of behavior therapy are provided in GSH, including stimulus control, self-monitoring, goal setting and contracting, strategies for managing high-risk situations, relapse prevention skills, and parent management skills training [58]. Self-monitoring is a fundamental aspect of self-regulation and includes observing and recording of eating and exercise behavior, and has been related to weight loss in children and adults [[59], [60], [61], [62], [63]]. In GSH, parents and children will receive “Habit Books,” and are instructed to record their dietary intake and physical activity each day. During each session, the health coach will review habit books and reinforce families for their efforts at any self-monitoring.

In addition to this skill, families will be introduced to stimulus control. Stimulus control aims to reduce environmental cues associated with calorie intake and inactivity, while also increasing environmental cues linked with healthy eating and physical activity. For example, to facilitate a change in dietary intake, families are encouraged to remove high calorie foods from the home, decrease restaurant eating, and to have a variety of fruit and vegetables easily accessible to children. GSH will also focus on setting both immediate and long-term goals. The health coach will encourage the use of proximal, realistic, and measurable goals. Progress towards goals will be evaluated at each meeting.

Parenting skills, as they apply to eating and exercise behavior, are included in the parent manuals only. These topics are derived from parent management training programs [64], and include information on modeling, positive reinforcement, and reward systems. Parent manuals provide suggestions for constructive methods of reviewing habit books with their children and provide examples of how to model healthy eating and physical activity behaviors for children. Motivation or reward systems include a point system in which the child earns points for meeting previously specified behavioral goals. After points are obtained, the child can trade them for rewards that parents and children mutually agree upon.

Towards the end of the intervention, parents will receive information on problem solving, planning ahead, high-risk situations, mastery of potential relapse occurrences, and the differences between lapses and relapses. Both parents and children will discuss how to problem solve and persist through relapses.

